### Study Design and Randomisation

The effect of the complex intervention, based around a training programme for GPs, will be evaluated in a cluster-randomised controlled trial with an intervention group and an active control group [37,40,41].

Each participating practice will form a 'cluster'. Practices will be randomised to participate in either intervention or control group. The randomisation of the GPs is stratified according to single-handed practice or group practice, gender (male/female/both sexes) and age (average age of participating GPs if more than one GP from a group practice participate), and urban or rural practice. Randomisation will be undertaken by random number generation, and allocations by a program made by an independent statistician will be concealed from those implementing the intervention. Both GPs and patients will be informed that the study investigates cardiovascular risk management but the patients will be 'blinded' to which group they are in.

In each group, 12 consultations will be observed and tape-recorded by a researcher (PK). The consultations will be divided between 4 GPs, each with 3 patients. The GPs will be selected according to gender and age (1 male + 1 female GP ≥ 48 years, 1 male GP + 1 female GP < 48 years). The patients from these 2×12 consultations will be interviewed immediately after the consultation and re-interviewed after 6 months. The interview will be of approx. 45 minutes duration. The tape-recorded consultation will be played back during the interview with the patient, using the Think Aloud-method [42,43]. The observations during the consultation will be written down as ethnographic field notes [44]. The aim is to make a rich and detailed 'thick' description [45] of the consultation. The patient interviews after the consultations will focus on the patients' immediate reactions to risk communication and decision-making in the consultation, using a semi-structured interview guide with open questions and play back of the tape-recorded consultation. The patients will be re-interviewed after 6 months.

Eight GPs from the intervention group will be interviewed in a focus group 6 months after participation in the workshop sessions. They will be selected according to gender and age (2 male + 2 female GP ≥ 48 years, 2 male GP + 2 female GP < 48 years). The purpose of the focus group interview is to get feedback on the intervention process and the training programme, with a particular view to examining their assessment of the risk communication tools developed for the intervention, to inform future implementation strategies.

The process and context of the RISAP-study will be investigated in detail using an action research approach [46-48]. It includes 'thick' ethnographic descriptions of the research process in order to describe and analyse the continuous critical reflection in the project group on research choices, adaptation of intervention model to the specific context, and conscious and pragmatic performance strategies in scientific and political communities and networks [49-51].

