### Outcome measurement

The patients will receive a questionnaire at baseline and after 3 and 6 months. It includes questions from validated scales: the Morisky Compliance Scale is used to assess adherence to chosen treatment, defined as 80% of the scheduled treatment taken as prescribed [52-54]. Self-rated health will be measured with questions from SF-12 [55-64], and patient enablement will be measured with the Patient Enablement Instrument [65]. Risk communication and decision-making effectiveness will be measured using the COMRADE scale [66]. In addition, the questionnaire will include questions on the patients' socio-demographic circumstances.

Prescriptions, contacts to the health services, and cholesterol level will be drawn from the register of the National Health Service of Denmark at baseline and at 6 months. The cholesterol level will be measured only on the GP's own initiative.

The GPs will receive a questionnaire at baseline and after 6 months about attitudes towards risk communication and cholesterol-reducing medication. After each consultation with a participating high cholesterol-patient, the GPs will complete a questionnaire about decision satisfaction with questions from the Provider Decision Process Assessment Instrument [67]. In addition, the GP will be asked to identify which, if any, risk communication tools were used during the consultation.

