### Sample size

A simulated power calculation shows that a trial with 40 practices in each group (at least 1 GP per practice and at least 7 patients with high cholesterol per GP) ensures a statistical power of 90% for detecting a 10% difference in lack of adherence (from 20% to 10%) at a significance level of 5%. The patients' adherence rates are assumed to vary from GP to GP according to a normal distribution on a logarithmic scale. The variance of the latent normal distribution is determined by assuming that 95% of the patients adherence levels within each GP vary within the intervals 0.08 to 0.50 (active control group) and 0.04 to 0.25 (experimental group).

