### Data analysis

Descriptive statistics will be generated for all variables. All analyses will be intention to treat. Data concerning adherence will be analysed by multivariate binomial regression with a latent variable with a level for each practice. Multivariate logistic regressions models will be used to determine variables independently associated with the outcome variable for questionnaire data. Missing responses will be excluded from the analysis. A probability level of p < 0.05 based on two-sided tests is considered statistically significant.

The qualitative research process will be iterative, alternating between data production, analysis, and theory. Informal analysis has been conducted in the developmental stage of the study and continues in a kind of funnel structure of "progressive focusing" [51]. The data from the interviews will be transcribed verbatim, and these transcriptions and written field notes will undergo a thematic analysis in which key patterns will be identified and grouped into themes [68]. The core themes and their meanings and interrelations will be explored and interpreted, using appropriate formal theories [69].

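### Randomisation is stratified on four practice factors, but the stated analysis names neither those factors nor the baseline scores as covariates; the cost is modest and the remedy nearly free

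*Protocol article*

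**What the plan says.** In the Protocol article, Study Design and Randomisation, the unit is the practice: "Each participating practice will form a 'cluster'. Practices will be randomised to participate in either intervention or control group". On stratification it says: "The randomisation of the GPs is stratified according to single-handed practice or group practice, gender (male/female/both sexes) and age", where age is averaged when several GPs from one practice take part, followed by "and urban or rural practice". The mechanism is given as: "Randomisation will be undertaken by random number generation, and allocations by a program made by an independent statistician will be concealed". No age cut-points or method of restriction within strata are given.

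Sample size plans "a trial with 40 practices in each group (at least 1 GP per practice and at least 7 patients with high cholesterol per GP").

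Data analysis says adherence will be analysed by "multivariate binomial regression with a latent variable with a level for each practice". Questionnaire data get multivariate logistic models whose stated purpose is to find which variables are independently related to outcome. Neither model has a covariate list.

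On baseline data, Outcome measurement says: "The GPs will receive a questionnaire at baseline and after 6 months about attitudes towards risk communication and cholesterol-reducing medication". Patients complete questionnaires, including SF-12 items, at baseline, 3 months and 6 months.

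**The concern.** Stratified allocation with restriction makes the arms alike on the stratifying factors. If those factors predict outcome, the true variance of the arm difference falls. A model that omits them still counts the between-stratum variation as noise (here it goes into the practice-level latent variable), so its standard error is larger than the design warrants. The test becomes conservative, and precision gained by design is not used.

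The questionnaire outcomes raise a second, separate matter. A model built to identify predictors does not by itself estimate an adjusted difference between arms. For SF-12 and GP attitudes, where a baseline value is collected, an arm comparison adjusted for that value is the natural analysis. The hypotheses include better self-rated health in the intervention group, so this comparison is one the trial intends to make.

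**Working it through.** **1. The plan's own figure.** Inputs from Sample size: 40 practices per arm, 7 patients per practice, non-adherence 20% against 10%, 5% significance (two-sided, from Data analysis), and 95% ranges across GPs of 0.08–0.50 and 0.04–0.25.

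- Centres on the log scale: √(0.08 × 0.50) = 0.20 and √(0.04 × 0.25) = 0.10, matching the stated rates.
- Log-scale SD: ln(0.50/0.08)/3.92 = 1.8326/3.92 = 0.4675. The second range gives the same value.
- Simulated power, random-intercept logistic model, likelihood-ratio test, 1,200 runs, no strata: 0.896. The stated 90% is reproduced.
- The same data analysed by a t-test on practice-level proportions: 0.874.

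**2. Number of cells.** The article gives no age bands, so two is assumed as the minimum.

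- Nominal: 2 (practice type) × 3 (gender) × 2 (age) × 2 (location) = 24.
- A single-handed practice cannot be of both sexes, so feasible cells are (2 + 3) × 2 × 2 = 20.
- 80/20 = 4 practices per cell. Three age bands give 5 × 3 × 2 = 30 cells, or 2.7 per cell.

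**3. Effect of omitting the strata.** The article does not say how prognostic the strata are, so the share of between-practice log variance they explain is assumed over 0–100%. Simulation set-up: 20 cells, 2 practices per arm in each cell (exact balance), practice-level tests, 20,000 runs. The adjusted test fits all cell terms, leaving 80 − 21 = 59 error degrees of freedom.

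| Share explained (assumed) | Type I error, unadjusted | Type I error, adjusted | Power, unadjusted | Power, adjusted | Change in points |
|---|---|---|---|---|---|
| 0% | 0.049 | 0.052 | 0.872 | 0.865 | −0.7 |
| 25% | 0.042 | 0.049 | 0.881 | 0.886 | +0.5 |
| 50% | 0.032 | 0.051 | 0.887 | 0.910 | +2.3 |
| 100% | 0.018 | 0.053 | 0.906 | 0.941 | +3.5 |

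The unadjusted test is conservative whenever the strata matter, and adjustment restores the nominal level. Exact balance within cells makes these figures close to the largest effect to expect.

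**4. Degrees of freedom with main effects.** The terms are practice type 1, gender 2, age 1 and location 1, so 5 in all. On a practice-level analysis this leaves 80 − 2 − 5 = 73, against 59 with cell terms. The loss when strata carry no information should therefore be no larger than the 0.7 points above. Main effects recover only the additive part of what the strata explain.

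**5. Baseline scores.** For a continuous score with baseline-to-follow-up correlation r, linear adjustment multiplies residual variance by 1 − r². With r assumed to be 0.5–0.6 this is 0.75–0.64. The formula holds for a linear model of a continuous score and does not carry over to a logistic model.

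**The case against.** The strongest reply is that this is a condensed article. Both models are called multivariate, no covariates are listed for either, and a covariate list commonly sits in the full protocol or analysis plan. A reader might infer that the strata and baseline values are excluded from the analysis. The text does not say so; it neither includes nor excludes them. That stands, and the point is therefore about what the stated analysis names. What remains is that the one structural feature given for the adherence model is the practice term, and the purpose given for the questionnaire models is not an arm comparison.

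A reader might also infer that about 4 practices per cell means balance is lost. This is not shown. With 20 equally likely cells, the simulated SD of the difference in arm size is 3.2 with blocks of 2 and 4.1 with blocks of 4, against √80 = 8.9 for simple randomisation. Sparse strata with blocks still balance better than no strata.

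The roughly 31% chance of a 45:35 or worse split applies only if there is no restriction at all, although the article says randomisation is stratified. It also concerns arm size, not covariate balance, and such a split costs little: (1/45 + 1/35)/(2/40) = 1.016, or 1.6% in variance. Nor does the text support a claim that minimisation is required. It would be a design preference, and the statistician's program may already restrict allocation.

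Finally, the planned 90% power is reproduced without strata in the model, so it does not depend on adjustment. That also stands.

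**Conclusion.** The point holds as a modest improvement to the analysis and does not threaten validity. If the strata are prognostic and allocation is restricted within them, omitting them lowers type I error to about 0.02–0.04 (strata explaining an assumed 25–100% of between-practice variance) and forgoes up to about 4 points of power. It introduces no bias. If allocation within cells were unrestricted, the conservatism would not arise.

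The figures rest on equal cells with exact balance, two age bands, practice-level tests in place of the latent-variable model, and an assumed prognostic strength that the article does not give.

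The baseline part is limited to outcomes with a true pre-intervention value, namely SF-12 and GP attitudes. It cannot extend to medication adherence, because patients already on cholesterol-reducing medication are excluded and so have no earlier adherence to adjust for.

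**What to change.** - In the adherence model and the other between-group models, state that practice type, gender mix, age and urban/rural location enter as main effects, alongside the practice-level term. Do not fit 20 cell terms, which would use far more degrees of freedom on 80 practices.
- State the analyses of SF-12 at 3 and 6 months and of GP attitudes at 6 months as comparisons between arms adjusted for the baseline score. Make this conditional on the baseline being completed before the consultation (patients) or before the training (GPs), and record that timing.
- If a fuller analysis plan already says this, confirming it is enough.

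The cost is wording and about 5 degrees of freedom. No new data are needed, and the change remains possible after allocation if it is fixed before outcomes are examined. The downside is a power loss of at most about 1 point if the strata prove unrelated to outcome.

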### Outcomes

The primary patient outcome is adherence to treatment choice. Secondary patient outcomes are self-rated health, anxiety, satisfaction with decision, enablement, satisfaction with communication, satisfaction and confidence in decision, and number of contacts to health services.

The primary GP outcome is satisfaction with decision.

Secondary GP outcomes are GP attitudes towards risk communication and towards preventive treatment of cardiovascular disease, patient involvement in decision-making, and use of risk communication tools.

### Outcome measurement

The patients will receive a questionnaire at baseline and after 3 and 6 months. It includes questions from validated scales: the Morisky Compliance Scale is used to assess adherence to chosen treatment, defined as 80% of the scheduled treatment taken as prescribed [52-54]. Self-rated health will be measured with questions from SF-12 [55-64], and patient enablement will be measured with the Patient Enablement Instrument [65]. Risk communication and decision-making effectiveness will be measured using the COMRADE scale [66]. In addition, the questionnaire will include questions on the patients' socio-demographic circumstances.

Prescriptions, contacts to the health services, and cholesterol level will be drawn from the register of the National Health Service of Denmark at baseline and at 6 months. The cholesterol level will be measured only on the GP's own initiative.

The GPs will receive a questionnaire at baseline and after 6 months about attitudes towards risk communication and cholesterol-reducing medication. After each consultation with a participating high cholesterol-patient, the GPs will complete a questionnaire about decision satisfaction with questions from the Provider Decision Process Assessment Instrument [67]. In addition, the GP will be asked to identify which, if any, risk communication tools were used during the consultation.

### Sample size

A simulated power calculation shows that a trial with 40 practices in each group (at least 1 GP per practice and at least 7 patients with high cholesterol per GP) ensures a statistical power of 90% for detecting a 10% difference in lack of adherence (from 20% to 10%) at a significance level of 5%. The patients' adherence rates are assumed to vary from GP to GP according to a normal distribution on a logarithmic scale. The variance of the latent normal distribution is determined by assuming that 95% of the patients adherence levels within each GP vary within the intervals 0.08 to 0.50 (active control group) and 0.04 to 0.25 (experimental group).

### Data analysis

Descriptive statistics will be generated for all variables. All analyses will be intention to treat. Data concerning adherence will be analysed by multivariate binomial regression with a latent variable with a level for each practice. Multivariate logistic regressions models will be used to determine variables independently associated with the outcome variable for questionnaire data. Missing responses will be excluded from the analysis. A probability level of p < 0.05 based on two-sided tests is considered statistically significant.

The qualitative research process will be iterative, alternating between data production, analysis, and theory. Informal analysis has been conducted in the developmental stage of the study and continues in a kind of funnel structure of "progressive focusing" [51]. The data from the interviews will be transcribed verbatim, and these transcriptions and written field notes will undergo a thematic analysis in which key patterns will be identified and grouped into themes [68]. The core themes and their meanings and interrelations will be explored and interpreted, using appropriate formal theories [69].

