**Methods/Design:**

The effect of the complex intervention, based around a training programme, will be evaluated in a cluster-randomised controlled trial with an intervention group and an active control group with 40 GPs and 280 patients in each group.

The GPs will receive a questionnaire at baseline and after 6 months about attitudes towards risk communication and cholesterol-reducing medication. After each consultation with a participating high cholesterol-patient, the GPs will complete a questionnaire about decision satisfaction (Provider Decision Process Assessment Instrument). The patients will receive a questionnaire at baseline and after 3 and 6 months. It includes questions about adherence to chosen treatment (Morisky Compliance Scale), self-rated health (SF-12), enablement (Patient Enablement Instrument), and risk communication and decision-making effectiveness (COMRADE Scale). Prescriptions, contacts to the health services, and cholesterol level will be drawn from the registers.

In each group, 12 consultations will be observed and tape-recorded. The patients from these 24 consultations will be interviewed immediately after the consultation and re-interviewed after 6 months.

Eight purposefully selected GPs from the intervention group will be interviewed in a focus group 6 months after participation in the training programme.

The process and context of the RISAP-study will be investigated in detail using an action research approach, in order to analyse adaptation of the intervention model to the specific context.

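### The model named for questionnaire outcomes, including the primary GP outcome, carries no practice term although practices are randomised

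*Protocol article*

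**What the plan says.** Study Design and Randomisation makes the practice the randomised unit: "Each participating practice will form a 'cluster'. Practices will be randomised to participate in either intervention or control group". The abstract plans "40 GPs and 280 patients in each group", and Sample size plans 40 practices per group, with at least one GP per practice and at least 7 patients per GP.

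Data analysis names two models in consecutive sentences. Adherence is to be analysed by "multivariate binomial regression with a latent variable with a level for each practice". The next sentence reads: "Multivariate logistic regressions models will be used to determine variables independently associated with the outcome variable for questionnaire data". It mentions neither practice nor GP. The section applies a two-sided 5% significance level throughout.

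Under Outcomes, "The primary GP outcome is satisfaction with decision". Outcome measurement explains how it is collected: "After each consultation with a participating high cholesterol-patient, the GPs will complete a questionnaire about decision satisfaction". The patient scales (SF-12, Patient Enablement Instrument, COMRADE) come from questionnaires sent to patients at baseline, 3 and 6 months.

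**The concern.** Patients of one practice share a GP and an allocation, and a GP who rates several consultations is the same rater each time. Such records are positively correlated within practice. A regression that treats them as independent understates the standard error of the group comparison, so intervals are too narrow and p-values too small.

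The article recognises this for adherence, both in the power simulation and in the analysis model. It does not carry it over to the other questionnaire outcomes. One of those is a declared primary outcome, and others bear on hypotheses in the Objective section (self-rated health, satisfaction with the decision). If the text is followed as it stands, these are tested at an error rate above the stated 5%.

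**Working it through.** **Inputs from the article.** There are 40 practices per group and at least 7 patients per GP, so m = 7 records per cluster with one GP per practice. Tests are two-sided at 5%. In Sample size, 95% of the GP-level rates lie between 0.08 and 0.50 (control) and between 0.04 and 0.25 (intervention), normal on the log scale. The midpoints on that scale are √(0.08 × 0.50) = 0.20 and √(0.04 × 0.25) = 0.10. These match the stated non-adherence of 20% and 10%, so the intervals are read as rates of non-adherence.

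**Reproducing the plan's power.** The log-scale SD is ln(0.50/0.08)/3.92 = 0.4675, and the intervention interval gives the same value. In simulations of 40 clusters of 7 per group with medians 0.20 and 0.10:

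- A random-intercept logistic likelihood-ratio test has 88.6% power (1,500 runs, Monte Carlo error about 0.8 points). A cluster-level t-test has 87.2% (20,000 runs).
- If 20% and 10% are read as means, the random-intercept test has 85.1%.

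The stated 90% is reproduced within 2 points on the median reading, so this reading of the variance assumption is sound.

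**ICC implied by the adherence assumptions (control).**

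- Mean = 0.20 × exp(0.4675²/2) = 0.223.
- Between-GP SD = 0.110.
- ICC = 0.110²/(0.223 × 0.777) = 0.070.

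The same steps for the intervention interval give an ICC of about 0.03.

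**Type I error without a practice term.** Design effect DE = 1 + (m − 1) × ICC. Actual error = 2 × [1 − Φ(1.96/√DE)].

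| ICC | Source | DE (m = 7) | True SE / unadjusted SE | Type I error |
|---|---|---|---|---|
| 0.01 | assumed | 1.06 | 1.03 | 5.7% |
| 0.02 | assumed | 1.12 | 1.06 | 6.4% |
| 0.05 | assumed | 1.30 | 1.14 | 8.6% |
| 0.07 | control-arm adherence spread | 1.42 | 1.19 | 10% |
| 0.10 | assumed | 1.60 | 1.26 | 12.1% |
| 0.20 | assumed | 2.20 | 1.48 | 18.6% |
| 0.30 | assumed | 2.80 | 1.67 | 24.1% |

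**Check by simulation.** With no true difference and the control-arm spread in both groups, logistic regression without a practice term rejects in 10.0% of 20,000 runs. With clustering allowed for, the rate returns to about 5%: 5.3% for the random-intercept test and 5.0% for the cluster-level t-test. Beta-binomial simulations at prevalences of 0.2 and 0.5 agree with the table to within about a percentage point.

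**Larger clusters.** If two GPs per practice give 14 records, DE = 1 + 13 × ICC. The error is then 12.7% at ICC 0.05 and 19.6% at ICC 0.10.

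**The case against.** The strongest reply is that silence is not exclusion. This is a condensed article, and random effects or robust standard errors are often left to a fuller document. That stands as a limit on certainty: the text does not rule out a practice effect. But the article does not simply leave the matter open. It names a model for each group of outcomes in adjacent sentences and gives the practice level to only one of them, and no other section supplies a clustered analysis for the rest.

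A second reply is that the sentence may describe an additional search for predictors rather than the group comparison. Its wording allows that. The article would then state no comparison model for the primary GP outcome, and the same sentence would still need to be clarified.

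Third, the ICC of 0.07 is borrowed from adherence, and at 0.01 or 0.02 the inflation is small. This is correct, and the result is therefore given as a range. A GP rating his or her own consultations could sit high in it, but that is an assumption.

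A reader might also infer three stronger points that the article does not support:

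- **Scale scores must be dichotomised.** Ordinal logistic regression needs no cut-point, and none is stated.
- **The reported quantity cannot be the intervention effect.** Randomised group may be one of the variables in the model, and nothing excludes it.
- **All outcomes are affected.** Adherence has its own practice-level model. GP attitude questionnaires, sent once per GP at each time point, are clustered by practice only where several GPs share one.

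**Conclusion.** The point holds on the plain reading of Data analysis. Per-consultation GP satisfaction and the patient scales are assigned to a model with no allowance for the randomised unit, so their p-values and intervals are too optimistic. With 7 records per cluster, the type I error of a nominal 5% test runs from about 5.7% to 24% over an assumed ICC range of 0.01 to 0.30. It is about 10% if these outcomes vary between practices as much as the plan assumes for control-arm adherence.

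The direction is firm for any positive ICC. The size is not, because the article gives no ICC for these outcomes. The primary patient outcome, which is the only one covered by the sample size calculation, is unaffected. The correction still matters because a declared primary outcome, GP satisfaction with the decision, falls under the unadjusted model.

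**What to change.** Revise the sentence in Data analysis to state that:

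- Each questionnaire outcome is compared between the randomised groups, with group as the effect of interest.
- The model allows for practice, through a practice random effect, generalised estimating equations or cluster-robust standard errors.
- A GP level is added only where a practice contributes more than one GP. With a single GP the two levels cannot be separated.
- A patient level is added if the repeated time points are modelled jointly.
- The model suits the scale of the outcome.
- Any search for associated variables is labelled exploratory.

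The cost is wording, a little more analysis work and slightly wider intervals. No extra patients or data are needed.

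### The Data analysis section names a practice-level term for adherence only; as written, the patient scales and the per-consultation GP satisfaction forms would be analysed without regard to the randomised clusters

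*Protocol article*

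**What the plan says.** The section Study Design and Randomisation makes the practice the cluster: "Practices will be randomised to participate in either intervention or control group". The Data analysis section then assigns models by type of data in two adjacent sentences. The first covers the primary patient outcome: "Data concerning adherence will be analysed by multivariate binomial regression with a latent variable with a level for each practice". The second covers the rest: "Multivariate logistic regressions models will be used to determine variables independently associated with the outcome variable for questionnaire data". The second sentence names no practice or GP level, and no other part of the article extends the practice term beyond adherence. The same section applies a two-sided 5% significance rule throughout.

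Among the outcomes left to the second sentence is one that is designated primary: "The primary GP outcome is satisfaction with decision". Under Outcome measurement it is collected after every study consultation, when "the GPs will complete a questionnaire about decision satisfaction with questions from the Provider Decision Process Assessment Instrument". The Abstract gives the size of the trial as two groups "with 40 GPs and 280 patients in each group", so on average each GP supplies 280 / 40 = 7 of these forms. The patient questionnaires (SF-12, Patient Enablement Instrument, COMRADE) come from the same groups of patients who share a GP.

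**The concern.** Arm is assigned by practice, so the information about the arm effect lies largely in the variation between practices. A logistic regression without a cluster term takes its standard error from the number of records instead. If records within a practice resemble each other at all, the standard error of the arm effect is too small, the p-value is too small and the interval is too narrow.

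The issue is plainest for the GP decision-satisfaction form, where one person rates about 7 consultations and has a personal level of satisfaction that carries over from one form to the next. The patient scales are exposed as well, because patients of one GP share that GP's way of communicating, which is what the training is meant to change. At stake is whether a result declared significant at 5% for the primary GP outcome or a secondary patient scale has anything close to a 5% false-positive risk.

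**Working it through.** **Inputs.** 40 practices per group, at least 1 GP per practice and at least 7 patients per GP (Sample size); 280 patients per group (Abstract); two-sided 5% (Data analysis); non-adherence 20% against 10%; 95% ranges between GPs of 0.08 to 0.50 (control) and 0.04 to 0.25 (experimental), normal on the log scale (Sample size). The article gives no ICC for any questionnaire outcome other than adherence.

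**1. The plan's own figure.** The log-scale SD is ln(0.50/0.08) / (2 × 1.96) = 0.4675, and the experimental range gives the same value. The medians are √(0.08 × 0.50) = 0.20 and √(0.04 × 0.25) = 0.10, which match the stated rates. Simulating 40 practices of 7 per group and testing with a random-intercept logistic model (likelihood-ratio test, 1,000 runs) gives power of 88.9% against the stated 90%. The stated power is therefore consistent with an analysis that has a practice-level term.

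**2. ICC implied by the adherence spreads.** With median q and log-SD σ, the mean is p = q·exp(σ²/2), the between-GP variance is p²(exp(σ²) − 1), and the ICC is that variance divided by p(1 − p).
- Control: p = 0.20 × 1.1155 = 0.223; variance = 0.0498 × 0.2443 = 0.01216; ICC = 0.01216 / 0.1733 = 0.070.
- Experimental: p = 0.1115; variance = 0.01244 × 0.2443 = 0.00304; ICC = 0.00304 / 0.0991 = 0.031.

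**3. Effect on an unclustered test.** With m = 7 records per practice, the design effect is DE = 1 + 6 × ICC. The unclustered standard error is 1/√DE of the correct one, and the true two-sided error at nominal 5% is 2 × P(Z > 1.96/√DE).

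| ICC | Source | DE | SE relative to correct | True error | Effective n of 280 |
|---|---|---|---|---|---|
| 0.031 | experimental-arm adherence spread | 1.18 | 0.92 | 7.2% | 236 |
| 0.070 | control-arm adherence spread | 1.42 | 0.84 | 10.0% | 197 |
| 0.2 | assumed | 2.20 | 0.67 | 18.6% | 127 |
| 0.3 | assumed | 2.80 | 0.60 | 24.2% | 100 |
| 0.5 | assumed | 4.00 | 0.50 | 32.7% | 70 |

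**4. Check by simulation.** Under no arm difference (20,000 trials, 40 × 7 per group), the unclustered logistic Wald test rejects in 10.1% of trials with the control-arm spread in both groups and in 7.0% with the experimental-arm spread. A t-test on practice proportions rejects in 5.1% in both cases. Beta-binomial data with mean 0.5 give 17.5%, 23.5% and 33.0% at ICC 0.2, 0.3 and 0.5, in line with the table.

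**The case against.** The strongest reply is that the article omits a cluster term and never says that clustering will be disregarded. It is a condensed article, and the error structure for secondary outcomes is often left to a fuller plan. A reader might infer that the authors have decided on an unclustered analysis; the text does not support that. What remains is the contrast: the preceding sentence does specify the practice level, so an analyst following the article would have reason to leave it out of the next model.

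Secondly, the sentence speaks of finding variables associated with the outcome and does not mention arm. It may describe an explanatory analysis. The figures above concern the arm comparison and would not carry over unchanged to covariates that vary within a practice. But shared-GP correlation would still have to be modelled, and the article would then state no arm comparison for the primary GP outcome, so the sentence needs correction on either reading.

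Thirdly, a reader might infer that every questionnaire outcome other than adherence is affected, on 280 records per group. That is too broad. GP attitudes are recorded once per GP at each time point, about 40 records per group. With one GP per practice there is no correlation between GPs to account for; it arises only where several GPs from one practice take part.

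Fourthly, the size is borrowed. The 0.070 comes from a different outcome and from the control arm, and the experimental arm implies less than half of that. The 19% to 33% range rests on an assumption that the article neither supports nor contradicts. These objections limit the size; for the arm comparison, they do not change the direction.

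**Conclusion.** The point holds in limited form. As written, the patient-level scales and the per-consultation GP satisfaction forms go into a logistic regression with no cluster term, although practices are randomised. For any positive ICC, the arm comparison then has standard errors and p-values that are too small and intervals that are too narrow. On the article's own adherence spreads, taken only as an illustration, the true error is about 7% to 10% and the standard error 8% to 16% too small, with 7 records per practice. For one GP's ratings the error would be 19% to 33% if their ICC were 0.2 to 0.5, which is an assumption.

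A reader might go on to doubt the main result of the trial. The article gives no ground for that here: the adherence model has its practice level, and the stated power refers to adherence and reproduces closely with such a model. The matter still deserves correction, because a designated primary GP outcome falls under the deficient sentence.

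**What to change.** Amend the questionnaire sentence in Data analysis to state that all analyses of patient-level and consultation-level questionnaire data account for practice, by a practice-level random effect as for adherence or by GEE with cluster-robust standard errors. Add a GP level within practice only where practices contribute more than one GP; with one GP per practice it coincides with the practice level and cannot be estimated separately. For GP attitudes, account for practice only where several of its GPs take part. Say also whether the sentence covers the arm comparison, an analysis of associated variables, or both.

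The cost is one sentence and wider intervals, by a factor of √1.18 = 1.09 to √1.42 = 1.19 at the illustrative ICCs, and more if one GP's ratings are strongly alike. No further data, practices or patients are needed.
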